### Sample size

2.5

Using the PDQ-39, a difference of 1.6 points in the overall score of this questionnaire is considered as clinically relevant [51]. In the current study, a difference of four points in the total score is expected to appear after intervention. A standard deviation of 15 was found in previous research [51]. This standard deviation is used to make a preliminary calculation of the sample size. Based on a significance of 5% and a power of 80%, a sample size of 198 subjects, separated into two groups of 99, is required to detect a clinically important difference between both groups. However, as the standard deviation might be different and due to the fact that the actual effect of a medication review is yet still unknown, an interim analysis will be performed after the inclusion of 2*25 patients and 3 months of follow up. This estimate will provide a more appropriate basis to determine the final sample size.

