### Safety reporting

2.6

All adverse events, defined as any undesirable experience occurring to a subject during the study, whether or not considered related to the experimental intervention, reported spontaneously by the subject or observed by the investigator or staff, will be recorded. Serious adverse events (SAEs) which are likely to be associated with the study intervention will be reported within 7 days after the responsible investigator has first knowledge of it. Due to the disease status and the advanced age of patients with PD included in this study, expected SAEs such as hospitalization and death may occur. Unlikely is that these SAEs are associated with participation in the study. To cover this, a six-monthly line listing will be provided to the Medical Ethical Review Board Twente. An annual safety report will be submitted to the accredited METC as well. A Data and Safety Monitoring Board was not installed.

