### Data analysis

2.7

Between-group differences in categorical variables will be analyzed using a Chi-square test or Fisher's exact test, as appropriate, while continuous variables will be analyzed using t-tests or a Mann-Whitney test, as appropriate. Continuous data will be presented as means with standard deviations (SD) in case of normal distributions or as medians with interquartile ranges (IQR) in non-normal distributions. For all continuous variables, a repeated measurement analysis will be performed to deal with possible missing data. According to the PDQ-39 manual, missing data will be imputed using Expectation Maximization [58].

The approach of a modified intention-to-treat analysis will be used, which essentially means that to include patients in this study, patients in the intervention group need to receive an SMR after baseline questionnaires are completed, and patients in the control group need to complete baseline questionnaires after randomization.

Secondly, a sensitivity analysis will be performed to measure the effects of an SMR in patients in whom at least one medication regimen change was implemented or to whom at least one recommendation has been given.

Data will be analyzed using SPSS version 24. P-values ≤ 0.05 are regarded as statistically significant. Data concerning the semi-structured interviews will be imported in and analyzed with Atlas Ti version 8.

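### The interim lets the treatment effect seen in 25 patients per arm help set the final sample size, which makes that size largely noise and leaves an ordinary 0.05 test above its nominal error rate

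*Protocol article*

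**What the plan says.** Section 2.5 of the protocol article plans 99 patients per arm. On the planning difference it says that "a difference of four points in the total score is expected to appear after intervention", and on variability that "A standard deviation of 15 was found in previous research". It calls the calculation preliminary and adds that "an interim analysis will be performed after the inclusion of 2*25 patients and 3 months of follow up".

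Two reasons are given. One is that the SD may turn out different. The other is that "the actual effect of a medication review is yet still unknown". The estimate from the interim is then to serve as the basis for fixing the final sample size.

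Section 2.7 (Data analysis) sets one threshold for the trial: "P-values ≤ 0.05 are regarded as statistically significant". It does not refer to the interim. Section 2.6 (Safety reporting) states: "A Data and Safety Monitoring Board was not installed".

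**The concern.** Re-estimating a sample size from the SD is routine and nearly harmless. Re-estimating it from the observed difference between arms is not, for two reasons.

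- **Noise.** Twenty-five patients per arm say very little about a 4-point difference when the SD is 15. A chance high result would shrink the trial and a chance low result would enlarge it many times over.
- **Error rate.** If the sample size depends on the interim difference and the final test pools all patients as if the size had been fixed, the test no longer has its nominal 5% error. Promising early results are preserved by stopping recruitment soon, and unpromising ones are diluted by more data.

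Section 2.5 names the unknown effect as a reason for the interim, and an interim can address that reason only by comparing the arms. At stake are the size of the trial and the validity of its primary test.

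**Working it through.** **Inputs.** From 2.5: difference 4, SD 15, significance 5%, power 80%, 99 per arm, interim at 25 per arm. From 2.7: final threshold 0.05. Assumed, because the article does not say: two-sided test, and the limits within which the sample size may move.

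**1. The plan's own figure.** n per arm = 2·SD²·(z₀.₉₇₅ + z₀.₈₀)²/δ² = 2·225·(1.960 + 0.842)²/16 = 450·7.849/16 = 220.7, so 221 per arm (442 in total). One-sided it is 174 per arm (348). The stated 99 is not reproduced. At 99 per arm, power for 4 points is 47% two-sided or 59% one-sided. The figure 99 does result with SD 10, or with a difference of 6.

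**2. Precision at the interim.** SE = 15·√(2/25) = 4.24. The 95% half-width is 2.011·4.24 = 8.5 points (48 df), more than five times the 1.6 points that the article treats as clinically relevant. If the true difference is 4:
- P(observed ≤ 0) = Φ(−4/4.24) = 17%; by symmetry P(observed ≥ 8) = 17%.
- P(observed < 1.6) = Φ(−2.4/4.24) = 29%.

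**3. What that does to the sample size.** With the formula in step 1 and SD 15, an observed 8.24 (one SE above 4) gives 52 per arm and an observed 1.6 gives 1,380. In simulation (true difference 4, observed effect and SD both used, assumed limits 25 to 400 per arm), the 10th to 90th percentile range is 38 to 400 per arm. There is a 33% chance of falling below 99.

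**4. Type I error of the unadjusted final test.** Simulation under no effect, two-sided t-test at 0.05. The symmetric rule resizes on the absolute difference. The one-directional rule sends the size to its maximum when the observed difference is not positive. The 3-to-6-month correlations are assumptions for the case where the interim uses 3-month data and the final test 6-month data.

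| Limits per arm | Rule | Same outcome at both looks | Correlation 0.8 | Correlation 0.6 |
|---|---|---|---|---|
| 25–400 | symmetric | 8.0% | 6.7% | 5.9% |
| 25–400 | one-directional | 6.5% | 5.8% | 5.5% |
| 99–400 | symmetric | 6.0% | 5.6% | 5.4% |
| 99–400 | one-directional | 5.5% | 5.3% | 5.2% |

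**5. The comparison that isolates the cause.** Resizing on the SD alone, with the difference held at 4, gives a type I error of 5.0–5.1%. The median size is 218 per arm, with a 5th to 95th percentile range of 153 to 300. The excess error therefore comes from using the effect.

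**The case against.** The strongest reply is that the article is a condensed account. It gives no formula, and its reference to the interim estimate is ambiguous: it could mean the SD, the effect or both. If only the SD were used, there would be almost nothing to correct. A floor, a cap or an adjusted final test may be set out in the full protocol or an analysis plan, so their absence here is no fault. The threshold in 2.7 is a general sentence for all tests.

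Much of this stands. Missing detail is not the point, and the size of the inflation cannot be fixed without the rule. What does not fall away is the stated purpose: an SD-only reading leaves the second reason for the interim with no function.

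Three stronger readings are tempting but not supported.

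- **That the trial team will see the unblinded comparison.** The article does not say who computes or sees the interim result. It reports only, under safety reporting, that there is no monitoring board, which does not exclude independent handling by a statistician.
- **That the error rate is 8%.** That value needs a size that can fall to 25 per arm, a rule that shrinks the trial for harmful trends too, and the same outcome at both looks. None of these is stated, and the abstract and 2.1 still aim for 200 patients.
- **That the interim is an early efficacy test.** No early stop is described, so error rates for two looks at 0.05 do not apply.

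**Conclusion.** The concern holds as a stated design choice: the observed effect, as well as the SD, is to inform the final sample size, and the article's only threshold is an unadjusted 0.05.

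The noise finding is the firmer part. The interim standard error (4.24) exceeds the planning difference (4) on the article's own SD, whatever the rule.

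The inflation is certain in direction for the effect-driven rules examined, but its size is conditional. It is roughly 5–6% if the size cannot fall below 99 per arm and roughly 6–8% if it can fall to the interim size. It is smaller in both cases if the final test uses 6-month data (down to about 5.2% and 5.5% at an assumed correlation of 0.6). A full protocol or analysis plan might already control it; this article does not.

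The 99 per arm is also not a sound anchor for any resizing rule, because it does not follow from the inputs given for it.

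**What to change.** Before any interim data are compared:

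1. Correct the planned size or its stated power. On the article's inputs, 80% power needs 221 per arm two-sided. If that is not feasible, restate the power (47% at 99 per arm) or the detectable difference (about 6 points at 99 per arm).
2. Delete the unknown effect as a reason to resize.
3. Re-estimate from the blinded SD of PDQ-39, both arms combined. Hold the planning difference at 4 points, compute no between-arm contrast, and allow no reduction below the corrected planned size.
4. If the effect must be used, have it handled by someone independent of the trial team and pre-specify a combination test for the final analysis.

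**Cost.** The sponsor gives up the early look at the effect. The wording change is small but its consequence may not be: if the SD is 15, an SD-only rule returns about 221 per arm, more than twice the current plan. The combined-arm SD also carries a little of the effect: with a true difference of 4 it is √(225 + 4²/4) = 15.13, which gives 450·(229/225)·7.849/16 = 224.7, or 225 per arm, a negligible increase. With 50 patients the SD itself is uncertain (95% interval about 12.5 to 18.7 when the estimate is 15, or 154 to 345 per arm), so the sponsor should decide in advance what maximum it can recruit.

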### Safety reporting

2.6

All adverse events, defined as any undesirable experience occurring to a subject during the study, whether or not considered related to the experimental intervention, reported spontaneously by the subject or observed by the investigator or staff, will be recorded. Serious adverse events (SAEs) which are likely to be associated with the study intervention will be reported within 7 days after the responsible investigator has first knowledge of it. Due to the disease status and the advanced age of patients with PD included in this study, expected SAEs such as hospitalization and death may occur. Unlikely is that these SAEs are associated with participation in the study. To cover this, a six-monthly line listing will be provided to the Medical Ethical Review Board Twente. An annual safety report will be submitted to the accredited METC as well. A Data and Safety Monitoring Board was not installed.

### Data analysis

2.7

Between-group differences in categorical variables will be analyzed using a Chi-square test or Fisher's exact test, as appropriate, while continuous variables will be analyzed using t-tests or a Mann-Whitney test, as appropriate. Continuous data will be presented as means with standard deviations (SD) in case of normal distributions or as medians with interquartile ranges (IQR) in non-normal distributions. For all continuous variables, a repeated measurement analysis will be performed to deal with possible missing data. According to the PDQ-39 manual, missing data will be imputed using Expectation Maximization [58].

The approach of a modified intention-to-treat analysis will be used, which essentially means that to include patients in this study, patients in the intervention group need to receive an SMR after baseline questionnaires are completed, and patients in the control group need to complete baseline questionnaires after randomization.

Secondly, a sensitivity analysis will be performed to measure the effects of an SMR in patients in whom at least one medication regimen change was implemented or to whom at least one recommendation has been given.

Data will be analyzed using SPSS version 24. P-values ≤ 0.05 are regarded as statistically significant. Data concerning the semi-structured interviews will be imported in and analyzed with Atlas Ti version 8.

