**Methods:**

In this multicenter randomized controlled trial we aim to enroll 200 PD patients from the outpatient clinic of three Dutch hospitals. Community pharmacists will perform a structured medication review in half of the assigned patients; the other half will receive usual care. Data obtained by use of six validated questionnaires will be collected at baseline and after 3 and 6 months of follow-up. Semi-structured interviews with community pharmacists will be conducted till data saturation has been reached.

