### Design

2.1

The study is designed as a multicenter randomized controlled trial (RCT) of a medication review intervention as one-time assessment in PD patients. We aim to enroll 200 patients with idiopathic PD from the neurology department of 3 Dutch hospitals (Medisch Spectrum Twente, Ziekenhuis Groep Twente and Isala hospital). Data obtained by use of validated questionnaires will be collected at baseline and after 3 and 6 months of follow-up (Fig. 1).

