### Recruitment, consent and randomization

2.2

In order to be eligible to participate, patients must meet the following criteria: (1) diagnosed with PD according to the UK-brain banking criteria [43]; (2) ≥ eighteen years of age; (3) ≥ four different medications daily; (4) ≥ four medication intake moments daily; (5) expressing motor and non-motor symptoms; (6) living (semi)-independent in the region of Enschede, Almelo, Hengelo or Zwolle; (7) be able to read and write the Dutch language. Exclusion criteria are: (1) being unable to administer their own medication, e.g. when requiring assistance from medical home care. PD patients receiving help from personal or family caregivers were not excluded based on this criterium; (2) having received a medication review within a year prior to the study; (3) having received a Deep Brain Stimulator, continuous duodopa gastro-intestinal gel therapy or continuous apomorphine therapy within a year before the study or willing to receive this within three months.

As soon as informed consent is obtained by the investigator and baseline measurements are performed, patients will be randomly assigned in a 1:1 ratio with a blinded blocked randomization with block sizes of four and eight. Inclusion is definite when patients in the intervention group complete the baseline measurements and receive an SMR, while patients in the control group only need to complete baseline measurements.

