#### Primary outcome

2.4.1

The primary outcome will be disease-specific quality of life, measured by the Parkinson's Disease Questionnaire-39 (PDQ-39). This validated and reliable instrument has 39 items comprising eight domains of health status: mobility, activities in daily living, emotional wellbeing, stigma, social support, cognitions, communication and physical discomfort [49,50]. It can be used to assess effectiveness of treatment, in which dimension scores are coded on a scale of 0–100 with a higher score indicating lower QoL [8]. A difference of 1.6 points in the PDQ-39 total score is required to pinpoint a clinically relevant difference or minimally important difference (MID) [51]. Depending on domain, MIDs vary between 1.8 and 11.4 points.

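### Section 2.7 names two analyses that both cover the primary PDQ-39, without saying which decides or giving the baseline PDQ-39 a role

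*Protocol article*

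**What the plan says.** All places are in the protocol article.

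- Section 2.4.1 sets the endpoint: "The primary outcome will be disease-specific quality of life, measured by the Parkinson's Disease Questionnaire-39 (PDQ-39"). It gives 1.6 points on the total score as the minimally important difference.
- Section 2.1 has the questionnaires "collected at baseline and after 3 and 6 months of follow-up".
- Section 2.7, on between-group differences: "continuous variables will be analyzed using t-tests or a Mann-Whitney test, as appropriate". Two sentences later: "For all continuous variables, a repeated measurement analysis will be performed to deal with possible missing data". Neither sentence names the PDQ-39, a visit, a contrast or a covariate. One significance threshold (P ≤ 0.05) covers everything.
- Section 2.5 expects that "a difference of four points in the total score is expected to appear after intervention", with SD 15, 5% significance, 80% power and 99 patients per group.
- Section 2.2 puts baseline first: "As soon as informed consent is obtained by the investigator and baseline measurements are performed, patients will be randomly assigned in a 1:1 ratio". Section 2.7, describing the modified intention-to-treat set, says "patients in the control group need to complete baseline questionnaires after randomization".

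**The concern.** The PDQ-39 is a continuous variable, so both sentences of section 2.7 apply to it. Three things are left open for the one outcome on which the trial will be judged.

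1. **Which analysis decides.** If the two disagree at the 5% level, the text gives no rule for the conclusion.
2. **Which scale the answer is on.** The choice between t-test and Mann-Whitney is left to what seems appropriate once data exist. A Mann-Whitney test gives no mean difference in points to set against the 4-point target or the 1.6-point threshold.
3. **What happens to baseline.** The repeated measurement analysis is given only a missing-data purpose. It could take baseline as a covariate, as one of the responses, or leave it out. These choices lead to different contrasts with different power.

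At stake are a single pre-stated answer in points, and precision that costs no extra data.

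**Working it through.** **Inputs.** From section 2.5: difference 4, SD 15 (not said whether of a single score or of a change; read here as a single score), 99 per group, 5% taken as two-sided. The correlation r between baseline and follow-up PDQ-39 is not in the document and is assumed over a range.

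**The plan's own figure.** n per group = 2 × [15 × (1.96 + 0.842) / 4]² = 220.7, so 221 per group and 442 in total. The stated 198 does not follow from its stated inputs. That is a separate issue. It matters here only because 47%, not 80%, is the starting point below.

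**Power formula** (normal approximation): Φ(effect / SE − 1.96), with SE = SD × √(2/99).

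**Unadjusted test of one follow-up score.** SE = 15 × √(2/99) = 2.132; 4 / 2.132 = 1.876; Φ(−0.084) = 46.7%. With the t distribution it is 46.3%.

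**Baseline as covariate, one follow-up score.** SD = 15 × √(1 − r²); the share of variance removed is r².

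- r = 0.5: SD 12.99, variance removed 25%, power 58%
- r = 0.7: SD 10.71, variance removed 49%, power 75%
- r = 0.8: SD 9.00, variance removed 64%, power 88%

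**Other contrasts that the wording allows.**

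- Change from baseline: SD = 15 × √(2(1 − r)).
- Group main effect averaged over all three visits, baseline included. This further assumes equal correlation r between visits and a constant 4-point effect at 3 and 6 months. No effect exists at baseline, so the expected contrast is 4 × 2/3 = 2.67 points, with SD = 15 × √((1 + 2r)/3). At r = 0.5, SD = 12.25, SE = 1.741, 2.67 / 1.741 = 1.532 and Φ(−0.428) = 33%.

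| Assumed r | Unadjusted, one visit | Baseline as covariate, one visit | Change from baseline, one visit | Group main effect, three visits incl. baseline |
|---|---|---|---|---|
| 0.5 | 47% | 58% | 47% | 33% |
| 0.6 | 47% | 65% | 56% | 31% |
| 0.7 | 47% | 75% | 68% | 29% |
| 0.8 | 47% | 88% | 84% | 27% |

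The last column falls as r rises, because averaging over correlated visits gains little while the effect stays diluted by a third.

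**Both follow-up visits averaged and adjusted for baseline.** Under the same equal-correlation and constant-effect assumptions, SD = 15 × √((1 + r)/2 − r²), giving power of 76%, 88% and 96% at r = 0.5, 0.7 and 0.8. If the effect differs between 3 and 6 months, these figures do not apply.

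**Timing of baseline.** Section 2.2 requires baseline measurements before random assignment. Section 2.7 has control patients completing the questionnaires after it. Allocation is not blinded (section 3), so a self-reported score given after assignment could reflect knowledge of the group. Adjustment is clean only with a pre-randomization baseline.

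**The case against.** A reader might infer that the plan makes an unadjusted t-test or Mann-Whitney test the primary PDQ-39 comparison, ignores baseline and so discards most of the available precision. The document does not support that.

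- The t-test sentence is generic. It continues the sentence on categorical tests and is not assigned to the primary outcome.
- The same paragraph promises a repeated measurement analysis for every continuous variable. With measurements at baseline, 3 and 6 months, that analysis may well use baseline. The text is silent on how; it does not say that baseline is left out.
- Removing more than half of the variance needs r above about 0.71. The document gives no correlation, and at r = 0.5 the share is a quarter.
- The gap between 47% and 80% comes from the sample-size calculation in section 2.5, not from the choice of test. That section also calls the calculation preliminary and plans to redetermine the sample size after 2 × 25 patients.
- A condensed article may leave model terms to an analysis plan that is not shown.

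All of this stands, and it limits the point. It does not remove it. The article is not merely brief: it states two analyses for the same primary outcome under one significance threshold and leaves the test type to the data. Nor does the phrase repeated measurement analysis settle the matter, since the contrasts it can denote have clearly different power.

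**Conclusion.** The point holds as one about the choice of analysis. Section 2.7 does not fix which of two stated analyses decides for the PDQ-39, and it gives the baseline PDQ-39 no stated role. Baseline adjustment would remove a share r² of the variance. On one follow-up score at 99 per group, that lifts power from about 47% to between 58% and 88% for r from 0.5 to 0.8. Across the contrasts tabulated, power ranges from about 27% to 88%.

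These figures rest on an assumed r, on SD 15 being that of a single score and on a two-sided 5% test. The three-visit column also needs equal correlations and a constant effect. If 15 is the SD of a change score, the adjusted figures do not apply. The direction is safer than the size: for any non-zero r, a baseline covariate reduces the residual variance. The change should be made, but the text does not show that the trial has committed itself to an unadjusted primary test. The sample-size discrepancy should be handled on its own.

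**What to change.** 1. Name one primary PDQ-39 analysis: a repeated-measures mixed model of the 3- and 6-month total scores, adjusted for baseline PDQ-39, with the deciding contrast stated (one visit, or the average of both). Further covariates, such as hospital, and the covariance structure are open to preference but should be fixed in advance.
2. Report the adjusted mean difference in points with a 95% confidence interval, read against 1.6 and 4 points.
3. Keep t-tests and Mann-Whitney tests for descriptive comparisons.
4. Use the same approach for the continuous secondary outcomes.
5. Reconcile sections 2.2 and 2.7 so that baseline is completed before randomization in both groups.
6. State which SD the interim re-estimation in section 2.5 uses, so that it matches the chosen model.

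The cost is wording in the analysis section or analysis plan. SPSS can fit the model and no new data are needed. If any control patients did complete baseline after assignment, their number should be reported.

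### The modified intention-to-treat set keeps intervention patients only if they receive the SMR, a post-randomisation condition that cannot apply to controls, and no analysis of all randomised patients is named

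*Protocol article*

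**What the plan says.** Section 2.2 (Recruitment, consent and randomization) fixes the order of events: "As soon as informed consent is obtained by the investigator and baseline measurements are performed, patients will be randomly assigned in a 1:1 ratio". The SMR is given to the intervention arm after that. The section then sets a different condition for each arm. For the intervention arm it states: "Inclusion is definite when patients in the intervention group complete the baseline measurements and receive an SMR". Of the other arm it asks less, since there "patients in the control group only need to complete baseline measurements".

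Section 2.7 (Data analysis) makes this the analysis population: "The approach of a modified intention-to-treat analysis will be used". It explains that "patients in the intervention group need to receive an SMR after baseline questionnaires are completed", and that "patients in the control group need to complete baseline questionnaires after randomization". On the order of baseline and randomisation for controls, this last clause disagrees with section 2.2.

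The only sensitivity analysis in section 2.7 looks at patients who had a regimen change implemented or were given a recommendation. The article names no analysis of all randomised patients. The Discussion states that the randomisation is not blinded. Section 2.2 does call the blocked randomisation blinded, but that can describe concealment of the sequence and does not mean that the arm stays unknown once assigned.

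**The concern.** A comparison is randomised only if the sets compared were formed by the randomisation. Here, an intervention patient who is randomised but never reviewed leaves the analysis. The control patient who would also have missed a review cannot be identified, and stays. The arms then differ by treatment and also by this selection.

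The article itself makes missed reviews plausible. Section 2.6 expects hospitalisations and deaths in this population. The Discussion describes the SMR as demanding in time and labour and poorly reimbursed. Delivery depends on each patient's own community pharmacist.

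Nothing else in the plan repairs this. Repeated-measures analysis and Expectation Maximization deal with missing values among patients inside the set, and these patients are outside it. The sensitivity analysis conditions on a further post-randomisation event and so narrows the set. Because the rule is written out twice, it is not a detail left for a fuller analysis plan to settle. At stake is whether the primary PDQ-39 result can be read as an effect of assignment to the SMR.

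**Working it through.** **Order of events.** Under section 2.2 the sequence is consent, baseline, randomisation, SMR. Baseline completion is then a pre-randomisation condition met by both arms, and SMR receipt is a post-randomisation condition on one arm. Under the control clause of section 2.7, baseline questionnaires follow randomisation, so some controls could be dropped too. They would be dropped on a different criterion from the intervention patients, so the arms would still not be comparable.

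**The plan's own figure.** The article gives no figure for the analysis set. The nearest one is the sample size in section 2.5: 99 per group for a difference of 4, SD 15, 5% significance and 80% power. The usual two-sided formula gives n = 2 × (1.96 + 0.8416)² × (15/4)² = 2 × 7.849 × 14.0625 ≈ 220.8, so 221 per arm. The stated 99 is not reproduced. That is a separate matter, and the bias below does not depend on it. I use 99 only as the planned number per arm.

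**Bias formula.** Let SMR recipients in the intervention arm have mean PDQ-39 μ and non-recipients μ + g (higher is worse), with no true treatment effect.

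- All randomised: (1 − p)μ + p(μ + g) = μ + p·g.
- Recipients only: μ.
- Spurious difference from dropping non-recipients in one arm: p·g.

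If the repeated-measures analysis compares change or adjusts for baseline, g is the gap in change (the part not explained by baseline), not the gap in level.

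**Inputs.** From the article: SD 15 and expected difference 4 (section 2.5), and minimally important difference 1.6 (sections 2.4.1 and 2.5). Assumed, because the article gives neither: p = 5–20%, and g = 3.75–15 points (0.25–1 SD).

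**Type I error** for an unadjusted comparison with 99 randomised per arm, nominal two-sided 5% and no true effect: SE = √{[225 − p(1 − p)g²]/[99(1 − p)] + 225/99}. For p = 20% and g = 15 this is √(189/79.2 + 225/99) = √4.659 = 2.158. The shift is 3.0/2.158 = 1.39 standard errors, and the rejection probability is 28.5%.

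| p | g (points) | Bias p·g | Share of 1.6 | Share of 4 | Type I error |
|---|---|---|---|---|---|
| 5% | 3.75 | 0.19 | 12% | 5% | 5.1% |
| 10% | 7.5 | 0.75 | 47% | 19% | 6.4% |
| 10% | 15 | 1.5 | 94% | 38% | 10.8% |
| 20% | 7.5 | 1.5 | 94% | 38% | 10.3% |
| 20% | 15 | 3.0 | 188% | 75% | 28.5% |

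If p = 0 or g = 0, the bias is 0.

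**Dilution under an as-randomised analysis.** If the expected 4 points refers to SMR recipients and non-recipients gain nothing, the effect becomes 4(1 − p): 3.6 points at p = 10% and 3.2 at p = 20%. The required number grows by 1/(1 − p)², that is 1/0.81 = 1.23 and 1/0.64 = 1.56. With SD 15 this is 273 and 345 per arm, against 221 without dilution.

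**The case against.** The strongest reply is that the problem may be small. Section 2.3 places the SMR at the start of the study, so the window for missing it may be short. Baseline PDQ-39 is measured, and if the analysis adjusts for it, stable frailty largely cancels and only a gap in change remains. On that scale 15 points is a full SD, so the upper rows of the table are extreme rather than typical. At the low end the bias is 0.19 points and the type I error 5.1%. SMR receipt is also a fairly objective criterion, and no discretionary exclusion is described. All of this stands as a limit on size. None of it makes the set a randomised one.

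A reader might go further than the article allows in four ways.

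- **That the bias favours the SMR.** It would if the patients missed are sicker or less engaged. They may instead be missed because of pharmacy workload, or decline because they have few problems, which would bring no bias or the opposite bias. The article does not settle this.
- **That every control is retained.** This follows under section 2.2 but not under the wording of section 2.7.
- **That follow-up visits are timed differently in the two arms.** The article states only baseline, 3 and 6 months and does not say what the visits are counted from, so there is nothing to correct there.
- **That the QALY and cost results are distorted by a known amount.** If they use the same set they inherit the problem, but nothing in the article allows its size to be calculated.

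An all-randomised set also does not recover later PDQ-39 scores for patients who die. Missing outcomes remain a separate problem in both arms.

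**Conclusion.** The point holds, and should be fixed before the analysis. As written, the primary set conditions on a post-randomisation event in one arm only, under open allocation, with no analysis of all randomised patients beside it. Confidence in that asymmetry is high because both sections state it.

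The size is conditional: about 0.2–3.0 PDQ-39 points over the assumed ranges of p and g, from well below to nearly twice the 1.6-point minimally important difference. The article does not support a claim that the bias is near 1.6 points or that it favours the SMR. It supports only the statement that the plan allows a bias of unknown size and direction, and provides no analysis that would reveal it.

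**What to change.** 1. In section 2.7, define the primary set as all randomised patients with a PDQ-39 completed before randomisation, analysed in the arm assigned, whether or not an SMR was delivered. Align the definition of inclusion in section 2.2 with this.
2. Reconcile the control clause of section 2.7 with section 2.2, so that baseline precedes randomisation in both arms and completing it is not itself a post-randomisation condition.
3. Keep collecting the 3- and 6-month questionnaires from intervention patients without an SMR, and report how many there were and why.
4. Keep the present set as a secondary analysis, labelled per-protocol.
5. In section 2.5, state whether the expected 4 points applies to all assigned patients or to SMR recipients. If the latter, state the as-randomised effect 4(1 − p) with the assumed p, and base the sample size on it.

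The running cost is small: a few more questionnaires and some dilution of the estimate. The planning cost is not negligible. If non-recipients gain nothing, the required number rises by about 23% at p = 10% and 56% at p = 20%.
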